**Figure 2 F2:**
[figure not shown]
**Recruitment and data collection procedures**.

Data collection for all measures and for participants in both conditions will occur at baseline and 12 weeks (on completion of the intervention). Participants in the intervention condition will be referred to the exercise program, whereas those in the control condition will receive usual advice about exercise from their clinician. Data collection will continue for participants in both conditions and for all measures except those of objective physical functioning at 6 months and 12 months.

For those in the intervention group, over the 12 week physical activity period, three morning and three afternoon sessions between Monday and Friday will be available for participants to attend. On commencement of the program, the project manager will provide a timetable of sessions that is convenient to the participant. The exercise physiologist will contact the participant 24 hours prior to their first physical activity session each week and remind them of their session times for the week. If the participant cannot be contacted, the exercise physiologist will contact the participant the day of their physical activity session to remind them of their session time. After two failed telephone attempts and if the participant does not attend the session, the participant will be declared 'absent' for the session. The total number of sessions attended by the participants will be recorded.

### Analysis

To address the primary aim of this study, we will conduct three main tests. To assess the impact of the intervention, we will perform an analysis of covariance (ANCOVA) on the post-intervention (12-week) physical activity levels of the participants in the two conditions, with their baseline scores as a covariate [53]. To determine the sustainability of the physical activity levels at 6 and 12 months, we will perform two ANCOVA on post-intervention (6 and 12 months, respectively) physical activity levels of the participants in the two conditions, with baseline scores as covariates.

To examine the data on the first of the secondary aims (determining the effect of the clinician referral and the physical activity program on psychological well-being, quality of life, and objective physical functioning) we will use the same analytical strategies as for the primary aim (ANCOVA with baseline scores as a covariates [53]). For this analysis, the dependent variables will be the subscales of the quality of life, anxiety, and depression measures, as well as the separate measures of objective physical functioning. The immediate effects of the intervention will be assessed using the 12-week data. The sustainability of the effects of the intervention on quality of life, anxiety, and depression will be assessed at 6 and 12 months.

To address the final aim, we will use path analyses to test for possible mediation of the intervention effect on level of physical activity based on the Baron and Kenny [54] approach. We will only test the components of SCT as possible mediators if they were affected by the intervention (i.e., group assignment) and associated with follow-up participation in physical activity. This approach requires that the outcome (i.e., participation in physical activity) be regressed on the proposed mediators (i.e. SCT components) and the intervention (i.e., group assignment coded as "0"= control and "1"= intervention). Mediation is present when the proposed mediator maintains a significant relationship with the outcome whereas group assignment does not. For the path analysis, we will adjust for the same variables as in the main analyses.

For all analyses, we will employ the intention-to-treat principle for all participants with available data at post intervention and follow-up.

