## Methods

### Design

This study is a cluster randomised controlled trial (RCT) to test the efficacy of an intervention, i.e., a clinician's referral to a physical activity program, to generate a) behaviour change (i.e., increasing physical activity levels) that is sustained over time and b) improved psychological well-being, quality of life, and objective physical functioning outcomes among prostate cancer survivors. The potential influence of individual and environmental mediators on participation in physical activity will also be determined.

Clinicians who agree to be involved in the study will be randomized into the intervention or control condition prior to the commencement of the study via computer-generated table of random numbers. Blinding of the clinician is not possible in this study, as one of our aims is to assess if the referral to the physical activity program by clinicians' influences the uptake of the physical activity program.

Our decision to undertake a cluster RCT, randomised by clinician with no cross over, was one based on the pragmatics of our situation. Our previous experience in this field suggests that it is difficult to gain support from busy clinicians if they were required to switch between both experimental conditions in the recruitment of patients [22]. Therefore, clinicians will be randomised into one of the two conditions and patients of each clinician will be regarded as separate clusters. There are likely to be up to twelve clinicians involved in this study (three clinicians from each of the three health services). Although we anticipate the effect of variation in the health services and in clinician physical activity recommendations on the key outcomes of this research to be very small, possible differences need to be taken into account through the use of clustering [23].

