### Participants

Eligible patients will be adult males who 1) have completed active treatment for prostate cancer within the previous three-12 months. Participants currently on hormone treatment will be eligible to participate; 2) were treated with curative intent, representing stages I, II, or III; and (3) have the ability to complete surveys in the English language. Patients will be excluded from this study if they have musculoskeletal, cardiovascular, or neurological disorders that could limit them from exercising. The patients' treating clinicians will assess their eligibility for the study.

The sample size for this study was calculated based on the primary research question; number of minutes of moderate or strenuous physical activity in a typical week in past month as measured by an adapted version of the Leisure Time Exercise Questionnaire at the completion of the 12 week intervention using the following assumptions: (1) a medium-sized effect will be found, (2) α will be set at .05, (3) power will be set at .80, (4) the attrition rate will be 10% at 12 weeks, and (5) the design effect will be 1.084. The anticipated effect size was judged from a similar project [24], where a medium-sized effect was found for the outcome of a physical activity intervention (*d *= 0.484), where the intervention group increase their total weekly minutes of physical activity by 59.3 minutes (SD = 126.6).

Physical activity levels will be measured at 12 weeks to answer the primary research question. An attrition rate of 10% is expected, based on our previous work in this area [22]. A design effect of 1.084 was included to account for clustering (ICC = .005, *m¯¬ *= 16.83). The ICC was estimated from a recently completed study investigating recruitment of newly diagnosed prostate and colorectal cancer patients (clustered by specialist) [22] and from published commentary in which the authors suggested that ICC rates of less than 0.01 have been found for practitioner prescribing rates [23]. The average size of each cluster (*m¯*) was calculated from an estimation of the number of participants needed in this study before the application of the design effect (*n *= 202) and the number of clinicians (clusters) involved in this research (*n *= 12). Based on these assumptions, 220 participants will need to be recruited.

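### Clinicians are randomised and the sample size allows for clustering, but the specified ANCOVAs name no adjustment for clinician

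*Protocol article*

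**What the plan says.** The Design section makes the clinician the unit of randomisation: "clinicians will be randomised into one of the two conditions and patients of each clinician will be regarded as separate clusters". It expects health-service and clinician effects on the outcomes to be very small, but still concludes that "possible differences need to be taken into account through the use of clustering". The Participants section carries this into the sample size: "A design effect of 1.084 was included to account for clustering", from an ICC of .005 and a mean cluster size of 16.83.

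The Analysis section then names the tests. For the primary aim at 12 weeks, "we will perform an analysis of covariance (ANCOVA) on the post-intervention (12-week) physical activity levels of the participants in the two conditions", with the baseline score as covariate. The 6- and 12-month analyses take the same form, again on "physical activity levels of the participants in the two conditions, with baseline scores as covariates". The secondary outcomes use the same strategy. The path analyses for mediation adjust for whatever the main analyses adjust for. The section names no clinician effect, cluster-robust variance, generalised estimating equation or cluster-level summary.

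**The concern.** Men who share a clinician share the randomised assignment, and their outcomes may be correlated. An ordinary ANCOVA on individual men takes its standard error from the variation between men and its degrees of freedom from the number of men. In this design the treatment contrast is between two small groups of clinicians. For any positive ICC the ordinary standard error is too small and the critical value too low, so p-values come out too small and intervals too narrow. The error favours declaring a benefit, and it affects the primary outcome at all three time points, every secondary outcome and the mediation models.

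The design effect does not repair this. It adds participants to protect power, but it leaves the standard error and reference distribution of the final test unchanged.

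**Working it through.** **Inputs**
- Analysed men: 220 recruited less 10% attrition at 12 weeks (Participants) = 198, taken as 99 per arm.
- Clinicians: k = 12, the number used in the sample size (Participants). The Design section's breakdown of three clinicians in each of three services gives 9, so 9 is shown as a secondary case.
- ICC: .005 is the protocol's value. The Participants section cites commentary putting ICCs for prescribing rates below .01. Values of .02 and .05 are assumptions to show the range.
- α = .05 (two-sided assumed, as sidedness is not stated) and d = 0.484 (Participants).
- Equal cluster sizes are assumed. With 9 clinicians the arms cannot hold equal numbers of clinicians, so those results are approximate.

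**1. The plan's own design effect.** 202/12 = 16.83, and 1 + 16.83 × .005 = 1.084, as stated. The usual form 1 + (m − 1) × ICC gives 1.079, a trivial difference. 202 × 1.084 = 218.97, consistent with the stated 220. Clustering does therefore enter the sample size.

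**2. Design effect in the analysed set.** DE = 1 + (m − 1) × ICC, with m = 198/12 = 16.5 or 198/9 = 22. At ICC .005:
- 12 clinicians: 1 + 15.5 × .005 = 1.0775
- 9 clinicians: 1 + 21 × .005 = 1.105

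**3. True size of the nominal 5% test.** Size = 2[1 − Φ(1.96/√DE)]. At ICC .005 with 12 clinicians, 1.96/√1.0775 = 1.888, which gives 5.9%.

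| ICC | DE, 12 / 9 clinicians | True size, 12 / 9 clinicians |
|---|---|---|
| .005 (protocol) | 1.0775 / 1.105 | 5.9% / 6.2% |
| .01 | 1.155 / 1.21 | 6.8% / 7.5% |
| .02 (assumed) | 1.31 / 1.42 | 8.7% / 10.0% |
| .05 (assumed) | 1.775 / 2.05 | 14.1% / 17.1% |

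The baseline-adjusted ANCOVA was also simulated with 12 clusters of 16 (20,000 runs per ICC, assumed baseline correlation 0.5). It rejected in 5.8%, 7.1%, 8.7% and 13.6% of runs at these four ICCs. A test on baseline-adjusted clinician means with 10 df rejected in 4.8% to 5.2%.

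**4. Width of a valid interval relative to the naive one.** Ratio = √DE × t(k − 2)/t(195). At ICC .005:
- 12 clinicians: 1.038 × 2.228/1.972 = 1.17
- 9 clinicians: 1.051 × 2.365/1.972 = 1.26

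Most of the widening comes from the small-sample critical value. √DE alone contributes only 4% to 5%.

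**5. Power of a valid analysis.** The non-centrality is 0.484/√(4 × DE/198), referred to t on k − 2 df. No gain from baseline adjustment is assumed.

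| ICC | 12 clinicians (10 df) | 9 clinicians (7 df) |
|---|---|---|
| .005 | 3.28, 84% | 3.24, 79% |
| .02 (assumed) | 2.98, 77% | 2.86, 69% |

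**The case against.** The strongest reply has three parts.

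First, the Design section commits the trial in principle to taking clustering into account. The Analysis section never says that men will be treated as independent, and an ANCOVA with a clinician effect or robust errors would not contradict its wording. The full analysis plan is not shown and may supply the term. A reader might infer that the trial has decided to ignore its clusters; the documents do not support that. They do show that the article states the unit, model, covariate and time points of its tests, and that this specification does not carry through the Design section. That is a method fixed badly. If an unseen plan adds an adjustment, the published text still has to be reconciled with it.

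Second, at the protocol's ICC the inflation is modest, about one percentage point. This stands, and it is the figure to lead with. A reader might take 14% or 17% as the trial's error rate, but those values rest on an assumed ICC of .05, ten times the protocol's. Larger ICCs are shown because .005 was taken from a study of recruitment and from commentary on prescribing rates, not from weekly minutes of activity.

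Third, adjustment with few clinicians is costly. This stands in part. It would be wrong to say that intervals become only slightly wider, since that counts the design effect and leaves out the critical value. The 9-clinician case depends on a separate inconsistency in the Design section and is secondary, because the sample size uses 12.

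**Conclusion.** The point holds. Followed as written, the specified tests are anti-conservative for any positive ICC, and nothing in the article corrects them. With 198 men and the protocol's ICC of .005, the true size is about 5.9% with 12 clinicians or 6.2% with 9. It reaches 6.8% at ICC .01 with 12 clinicians and goes higher only under assumed ICCs. These figures assume equal clusters and a two-sided test.

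A reader might also infer that a valid analysis would leave the trial underpowered. At the protocol's ICC the documents do not support that, since the stated 80% is met with 12 clinicians and missed by about one point with 9. The shortfall becomes material only at a larger assumed ICC such as .02. The correction should nevertheless be made before analysis, because it concerns the validity of the primary test and should not depend on a borrowed ICC being right.

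**What to change.** Carry the Design section's commitment into the Analysis section. Specify a baseline-adjusted analysis that accounts for clinician with small-sample inference. Two examples would do:
- a linear mixed model with condition and baseline score as fixed effects, a random clinician intercept, and Kenward-Roger or Satterthwaite degrees of freedom; or
- a baseline-adjusted cluster-level test on clinician means with k − 2 df.

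Report the estimated ICC, and apply the same approach to the 6- and 12-month, secondary and mediation models.

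A health-service term is optional, as the article states no stratification by service. With three services it uses two more between-cluster df, leaving about 8 (12 clinicians) or 5 (9). Critical values become 2.31 and 2.57, and power at ICC .005 falls to about 82% and 74%.

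The change needs no new data or patients. Its cost is the wider interval and the power shown in the working.

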### Study aims and hypotheses

The primary aim of the ENGAGE study is to compare the efficacy of a clinician referral and 12-week, supervised, exercise physiologist-led physical activity program compared to usual care (no referral to the physical activity program and typically minimal advice about physical activity) in improving the physical activity levels of prostate cancer survivors at three post-intervention time points:12 weeks, 6 months, 12 months. We hypothesise that participants in the intervention condition will be more physically active than participants in the control condition.

A secondary aim is to determine the effects of the clinician referral and physical activity program on the psychological well-being, quality of life and objective physical functioning of prostate cancer survivors. At the three post-intervention time points (12 weeks, 6 months, 12 months), we hypothesise that the clinician referral and physical activity program will improve participants' quality of life and decrease anxiety and depressive symptoms over and above changes on such measures that participants in the control condition may experience at post intervention. We will measure objective physical functioning at baseline and 12 weeks only, and hypothesise that participants in the intervention condition will improve their exercise capacity more than those in the control condition.

A further aim is to assess the impact of the intervention on main health determinants using the social cognitive theory and whether these determinants mediate behaviour change. We hypothesise that the intervention will have positive effects on self-efficacy, outcome expectations, goals, and socio-structural factors; and that self-efficacy will have a direct association with physical activity and an indirect association, mediated by outcome expectations, goals, and socio-structural factors.

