### Physical Activity Program

Participants will initially undertake a one-on-one session with the exercise physiologist, which will involve a discussion of each participant's beliefs in his or her ability to be physically active, physical activity preferences, outcome expectations, goals, and strategies for using facilitators and overcoming barriers to performing physical activity. The topics for this discussion are based on the concepts (previously identified) within social cognitive theory that are particularly relevant to health behaviour [19,20]. This is to increase long-term adherence to physical activity.

Emphasis will be placed on exercise physiologists regularly counselling participants throughout the structured physical activity sessions. The counselling topics will be based on the constructs of social cognitive theory. Exercise physiologists involved in this study will be trained in the application of social cognitive theory to physical activity uptake and adherence for survivors of prostate cancer. Exercise physiologists will be provided with checklists to ensure that they are regularly discussing key factors, including setting goals, aligning activity with outcome expectations, overcoming barriers and drawing on facilitators.

Based on previous work with prostate cancer patients [25], participants will undertake a 12-week program that will include supervised physical activity sessions and unsupervised physical activity. During the supervised sessions, several participants may be exercising at the same time. As participants will enter and leave the program at varying times and will have different weekly schedules, no attempt will be made to allocate participants to groups that will train in 12-week blocks. The physical activity program will be tailored to suit the ability of each participant. Exercise physiologists will lead two supervised sessions per week and will advise participants on what physical activity to undertake during their one non-supervised session per week.

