### Primary Outcome

Our primary outcome is the number of minutes of moderate-and strenuous physical activity per week as measured by an adapted version of the Leisure Time Exercise Questionnaire [32]. In this questionnaire, participants are asked to report the average weekly frequency and duration with which they engaged in strenuous, moderate, and light exercise over the past month. Consistent with a change made to the questionnaire in a study of colorectal cancer survivors [33], participants were asked to report the average duration of time they spent exercising at each intensity, in addition to the frequency. In addition, some of the physical activities were deleted from the instrument, because they were not common activities in Australia (e.g., horseshoes, snowmobiling). The validity and reliability of the Leisure Time Exercise Questionnaire compares favourably with other physical activity questionnaires [34].

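### The mediation rule requires a non-significant group effect, so it rejects a real partial mediator whenever the remaining direct effect is detected

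*Protocol article*

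**What the plan says.** The Analysis section of the protocol article sets out the mediation analysis in four steps.

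- Method: "we will use path analyses to test for possible mediation of the intervention effect on level of physical activity based on the Baron and Kenny" approach.
- Entry condition: "We will only test the components of SCT as possible mediators if they were affected by the intervention" and are associated with activity at follow-up.
- Model: the outcome is to "be regressed on the proposed mediators (i.e. SCT components) and the intervention", with group coded 0 or 1 and the same adjustment variables as in the main analyses.
- Decision: "Mediation is present when the proposed mediator maintains a significant relationship with the outcome whereas group assignment does not".

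The section has no category for partial mediation, and it mentions no estimate, test or interval for the indirect effect.

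The related hypothesis, under Study aims and hypotheses, is that "self-efficacy will have a direct association with physical activity and an indirect association, mediated by outcome expectations, goals, and socio-structural factors".

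Two other statements bear on whether a direct effect is likely. Under Physical Activity Program: "Exercise physiologists will lead two supervised sessions per week". Under Primary Outcome, participants are asked to "report the average weekly frequency and duration with which they engaged in strenuous, moderate, and light exercise over the past month".

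**The concern.** A non-significant coefficient does not show that an effect is absent. The criterion nevertheless makes non-significance of the group term a condition for mediation. A construct that carries part of the intervention effect then passes or fails according to whether the rest of the effect happens to reach significance. That depends on sample size and noise as well as on the mechanism.

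A direct effect is plausible here. Two supervised sessions of about 50 minutes give about 2 × 50 = 100 minutes of supervised exercise a week, although not all of it need count as moderate or strenuous. The 12-week questionnaire looks back one month, so it covers that period. Attending booked and reminded sessions can raise reported minutes without any change in self-efficacy, expectations or goals. This route applies to the 12-week outcome; at 6 and 12 months the supervised sessions are over.

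At stake is the further aim of the trial, which the Discussion presents as a strength: learning how the behaviour change comes about. A real mechanism could be reported as absent.

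**Working it through.** **Inputs.** The article gives no figure for the mediation analysis, so there is none to reproduce. From the sample size paragraph under Participants come 220 recruited, 10% attrition at 12 weeks, α = .05 (taken as two-sided) and d = 0.484. Analysed: 220 × 0.90 = 198. The path values are assumptions.

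**Model.** Equal arms and residual SD 1. Path a is the effect of group on the mediator, b the effect of the mediator on activity given group, and c′ the direct effect of group given the mediator. The total effect is a × b + c′.

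- Stated rule: a significant, b significant, c′ not significant.
- Comparison: a significant and b significant.

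Every trial that passes the stated rule also passes the comparison. The extra condition can therefore only remove detections.

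**Hand check.** Take a = 0.5, b = 0.4, c′ = 0.284, so the total is 0.5 × 0.4 + 0.284 = 0.484. Expected standard errors with N men:

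- SE(a) = 2/√N = 2/√198 = 0.142; z = 0.5/0.142 = 3.52; power about 0.94.
- SE(b) = 1/√N = 0.071; z = 0.4/0.071 = 5.6; power about 1.
- SE(c′) = 2√(1 + a²/4)/√N = 0.1465; z = 0.284/0.1465 = 1.94; power about 0.49.

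Comparison: about 0.94 × 1 = 94%. Stated rule: about 0.94 × (1 − 0.49) = 48%.

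With N = 600, SE(c′) = 0.0842, z = 3.37 and power is about 0.92. The stated rule falls to about 1 × (1 − 0.92) = 8%, while the comparison reaches 100%.

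**Simulation at N = 198** (3,000 to 20,000 trials per row; repeat runs differ by a point or two):

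| Assumed truth | a | b | c′ | Stated rule | Both paths tested |
|---|---|---|---|---|---|
| About 21% mediated | 0.5 | 0.2 | 0.384 | 21–22% | 74–75% |
| About 41% mediated | 0.5 | 0.4 | 0.284 | 48–50% | 94% |
| Half mediated | 0.5 | 0.513 | 0.2565 | 55% | 94% |
| Half mediated | 0.8 | 0.33 | 0.264 | 60% | over 99% |
| About 75% mediated | 0.8 | 0.5 | 0.133 | 86–87% | 100% |
| Two mediators | 0.5 each | 0.4 each | 0.084 | 85–86% | 94% |
| Fully mediated | 0.5 | 0.484 | 0 | 89% | 94% |

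Share mediated is a × b divided by the total; for the first row, 0.10/0.484 = 21%. In the two-mediator row the rates are for one of the mediators. The fully mediated row has a smaller total effect (0.242) than the others.

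**Stated rule as N changes:**

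| Assumed truth | 100 | 198 | 400 | 800 | 1600 |
|---|---|---|---|---|---|
| Half mediated, a = 0.5 | 54% | 55% | 30% | 6% | 0.2% |
| About 75% mediated | 88% | 86% | 76% | 59% | 31% |
| Fully mediated | 65% | 89% | 95% | 95% | 95% |

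In the half-mediated case, testing both paths rises from 70% at N = 100 to 99.9% at N = 400.

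**Limits.** Apart from the two-mediator row, there is one mediator. No baseline covariate is included and clustering is ignored.

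**The case against.** The best defence is that the size is not fixed by the document and may be modest. The model takes several constructs together, and several mediators absorb more of the group effect. With two mediators the gap at N = 198 is about 9 points (85% against 94%), and at N = 600 the rule still succeeds in 82% of trials. The trial is also planned at 220 men, so results at 600 or more show a property of the rule and are not a forecast for this trial. All of this stands, and it is why a range is given.

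Four stronger readings are tempting, and the article does not support them.

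- **That the rule always finds less mediation as data improve.** This holds only while a direct effect remains, and even then the rate can be flat at small N (54% and 55% at 100 and 198). Under full mediation it rises to about 95%.
- **That the self-efficacy hypothesis goes untested because only one regression is planned.** The article names path analyses, and the regression is described as what the approach requires. Whether the chain from self-efficacy through the other constructs is fitted may be left to the full protocol or analysis plan.
- **That the entry condition is itself a fault.** Requiring the intervention to affect the mediator is a test of path a, which the comparison imposes too.
- **That an undetected direct effect would be reported as full mediation.** The criterion says only that mediation is present and attaches no label of full or partial.

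None of this rescues the decision sentence. It is a stated criterion, so an analysis plan that handled partial mediation properly would have to depart from it.

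**Conclusion.** The point holds for the decision rule. As written, the rule takes a non-significant group coefficient as evidence of no direct effect and rejects a real partial mediator whenever the direct effect is detected. With a remaining direct effect, the chance of rejection tends to 100% as precision grows.

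At about 198 men, under the assumed paths, real partial mediation is found in roughly 20% to 87% of trials, against about 74% to 100% when paths a and b are both tested. The loss is largest when the mediator carries a small share of the effect. It is small when mediation is nearly complete or when several mediators share the effect. No single figure within that range can be claimed, because the article gives no path values.

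Only the mediation aim is affected. The primary and secondary ANCOVAs do not use this rule.

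**What to change.** In the Analysis section, remove the condition that group assignment be non-significant. For each construct, base the conclusion on the estimated indirect effect (a × b) with a 95% bootstrap or Monte Carlo interval that respects the clinician clusters. Report the direct effect with its interval beside it, so that partial mediation can be seen as such.

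The cost is a change of wording and a little more analysis. The mediators and the activity outcome are already scheduled at baseline, 12 weeks, 6 months and 12 months, so no new data are needed.
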